### Subgroup analysis

The primary endpoint of subclinical congestion at discharge will be evaluated by baseline left ventricular ejection fraction (<50% and >50% or greater), sex, comorbidities, cardiomyopathy aetiology, and age >70 years or <70 years.

### Allocation concealment and masking procedures

Lung and IVC ultrasound will be performed to all the patients, and patients will be blinded to the group assigned. The treating medical team will be blind to the results of the ultrasound of the control group. The independent clinicians adjudicating 90-day events will not participate in patient follow-up and will be blind to the assigned group.

### Statistical analysis plan

According to our preliminary pilot data derived from a sample of 20 patients during the new ultrasound tool proof trial, 70% had >5 B-lines and/or dilated IVC at discharge with the usual care strategy at our hospital. Therefore, to reach a relative risk reduction of 50% (ie, 70% in usual care and 35% in the CAVAL US-guided strategy), setting a power of 80% and a two-sided type I error rate of 5%, we will need 29 patients in each arm to accomplish our hypothesis.

Analysis will be performed by intention to treat. Continuous variables will be expressed as mean and SD, or median and IQR, according to their distribution. Normality of distribution of variables will be assessed using the Kolmogorov-Smirnov test or the Shapiro-Wilk test, according to the sample size. Continuous variables will be compared using the Student’s t-test or the Mann-Whitney U test, as applicable. Categorical variables will be presented as numbers and percentages. The Χ^2^ test or Fisher’s exact test will be used to compare proportions. No imputation will be made for missing data.

The Kaplan-Meier method will be used to analyse time-to-first event data. The differences in time-to-event distributions will be evaluated using the log-rank test. Univariate HRs with associated 95% CIs will be estimated for the composite primary endpoint and secondary endpoints and derived from the Cox proportional-hazards model; however, multivariate Cox regression analysis will only be used if there are important prognostic factors or patients’ baseline characteristics exhibiting significant imbalance between the two groups established by randomisation. In all cases, the alpha error will be set at 5% to establish statistical significance. All the statistical calculations will be performed using SPSS V.24 software package.

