### Participants and eligibility

Patients admitted with AHF in a private cardiovascular centre in Buenos Aires, Argentina. Eligibility criteria for participants are described in box 1.

Box 1Eligibility criteriaInclusion criteria (all of them)Hospitalisation of 24 hours or more for decompensated heart failure (HF) defined as new onset of symptoms or worsening of previous symptoms (including orthopnoea, progression to functional class New York Heart Association III–IV, bendopnoea or fatigue) or signs of volume overload.Jugular venous distension, hepatojugular reflux, lower extremity oedema or signs of pulmonary congestion.Chest X-ray with signs suggestive of pulmonary congestion.Elevated pro-B-type natriuretic peptide levels of 450 pg/mL, 900 pg/mL and 1800 pg/mL for ages <50 years, 50–75 years and >75 years, respectively, within 24 hours of admission.^53^
^54^
Sufficient ultrasound visualisation to assess inferior vena cava and lungs.Exclusion criteria (any of them)Not willing to participate.Life expectancy of less than 6 months.Uninterpretable lung or inferior vena cava ultrasound.Transfer to another hospital before hospital discharge.Systolic blood pressure <90 mm Hg.Chronic kidney disease (creatinine clearance <30 mL/min calculated with the Modification of Diet in Renal Disease (MDRD) study equation or haemodialysis).Requirement for invasive or non-invasive ventilator support.Pregnancy.Low cardiac output syndrome/cardiogenic shock.Death during index hospitalisation.Acute coronary syndrome, myocardial revascularisation or heart valve replacement within the previous 3 months.Being on heart transplant waiting list.Cardiac resynchronisation therapy device implanted within the previous 3 months.Severe tricuspid valve regurgitation.HF secondary to causes amenable to invasive correction: cardiac surgery, percutaneous interventions or pacemaker implantation.HF secondary to significant arrhythmias (advanced atrioventricular block or sinus arrest, sustained ventricular tachycardia or any sustained arrhythmia other than atrial fibrillation causing haemodynamic instability according to the discretion of the treating physician).HF secondary to severe systemic infection.Severe psychiatric illness.Palliative care.SARS-CoV-2 infection.

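### The 29 patients per arm come from a formula that matches neither named test; power is about 77% with chi-square, not 80%, with no allowance for loss.

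*Protocol article*

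**What the plan says.** All planning figures are in the protocol article, Statistical analysis plan section, unless another place is named.

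- **Control rate.** In a pilot sample of 20 patients, "70% had >5 B-lines and/or dilated IVC at discharge with the usual care strategy at our hospital".
- **Effect.** A "relative risk reduction of 50% (ie, 70% in usual care and 35% in the CAVAL US-guided strategy").
- **Error rates.** The calculation is described as "setting a power of 80% and a two-sided type I error rate of 5" per cent.
- **Result.** From these, "we will need 29 patients in each arm to accomplish our hypothesis". The Abstract randomises 58 patients, and the Randomisation section fixes 1:1 allocation.
- **Test.** A chi-square test or Fisher's "exact test will be used to compare proportions". The text does not say which applies to the primary endpoint.
- **Missing data.** "No imputation will be made for missing data".
- **Patients who may have no endpoint.** Randomisation is within 24 hours of admission, and the endpoint is read at discharge. Box 1 lists as exclusions both death during the index stay and "Transfer to another hospital before hospital discharge". Either can become known only after randomisation.

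**The concern.** A sample size supports a stated power only for the test that will be used. Here the size rests on an unpooled variance. The Pearson chi-square uses a pooled variance under the null hypothesis, and Fisher's test is conditional and more conservative. If neither reaches 80% at 29 per arm, the article claims a power that its own analysis does not have.

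Two further features bear on this. The choice between the tests is open, and at this size it moves both power and type I error noticeably. The number randomised also equals the number the formula requires, so every patient must have a usable discharge scan for even the recomputed power to apply.

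No result would be invalidated. What is at stake is the accuracy of a stated design property in a 58-patient trial with one binary primary endpoint.

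**Working it through.** **Inputs (article, Statistical analysis plan and Randomisation):** p1 = 0.70, p2 = 0.35, difference d = 0.35, mean rate 0.525, two-sided alpha 0.05 (z = 1.960), power 0.80 (z = 0.8416), allocation 1:1.

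**1. Reproduce the plan's figure (unpooled variance).**

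n = (1.960 + 0.8416)² × [0.70 × 0.30 + 0.35 × 0.65] / 0.35² = 7.849 × 0.4375 / 0.1225 = 28.03, rounded up to 29. This is the stated number.

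**2. Formula matching the Pearson chi-square (pooled under the null).**

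n = [1.960 × √(2 × 0.525 × 0.475) + 0.8416 × √0.4375]² / 0.1225 = 30.75, so 31 per arm.

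**3. Formula approximating Fisher's test (continuity correction).**

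n = (30.75 / 4) × [1 + √(1 + 4 / (30.75 × 0.35))]² = 36.2, so 37 per arm.

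**4. Exact power.** For each pair of counts, multiply the two binomial probabilities and add up those where the two-sided p-value is at most 0.05.

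| Evaluable per arm | Pearson chi-square, uncorrected | Fisher |
|---|---|---|
| 29 / 29 | 77.4% | 68.4% |
| 30 / 30 | 79.8% | 71.4% |
| 31 / 31 | 81.9% | 74.1% |
| 37 / 37 | 86.6% | 80.6% |

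The normal approximations at 29 per arm agree: 77.5% (pooled) and 68.3% (continuity-corrected). The shortfall against 80% is 2.6 points with chi-square and 11.6 points with Fisher.

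**5. Which test is likelier.** At the planning rates the smallest expected cell count is 29 × (1 − 0.525) = 13.8. The usual small-count reason for Fisher would not arise.

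**6. Loss.** 58 = 2 × 29, so there is no inflation. The article gives no loss rate; the losses below are assumptions.

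| Evaluable | Patients lost | Chi-square | Fisher |
|---|---|---|---|
| 28 / 28 | 1 per arm | 75.1% | 65.7% |
| 27 / 27 | 2 per arm (2/29 = 7%) | 72.4% | 62.6% |
| 26 / 26 | 3 per arm (3/29 = 10%) | 71.4% | 62.3% |
| 29 / 28 | 1 in the intervention arm | 80.4% | 71.9% |
| 28 / 29 | 1 in the control arm | 80.0% | 71.4% |

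Exact power moves in steps because the counts are discrete, so a one-patient imbalance can raise it. The smooth pooled approximation does fall: 75.3% at 5% loss and 72.9% at 10%.

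**7. Exact type I error.** At 29 / 29 with a common rate of 52.5%, it is 4.8% for the uncorrected chi-square and 2.5% for Fisher. Over other common rates the chi-square reaches about 5.5% at 29 / 29 (near 0.12 and 0.88). At 29 / 28 and 52.5% it is about 6.2%. The 80% at that split is therefore reached only by exceeding the stated 5%.

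**The case against.** **The number is correct.** Twenty-nine is what a standard textbook formula returns, and the difference from the pooled formula is two patients per arm. This stands. A reader might infer an arithmetic slip; the documents do not support that. The mismatch is between formula and test.

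**The gap is small beside the uncertainty in the inputs.** The 70% rests on 20 patients; 14 of 20 has an exact 95% interval of about 46% to 88%. With the halving held, exact chi-square power at 29 per arm is 70.7% for a 65% control rate, 79.9% for 72% and 83.5% for 75%. The Introduction calls the study a pilot trial, and the Discussion concedes that expert care may reduce power. This stands and limits the weight of the point. It does not make 80% the right figure for the rates the article chose.

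**The Fisher figure is largely hypothetical.** Naming both tests is common shorthand for using Fisher when expected counts are small, and the selection rule may be in a document not shown. This mostly stands. A reader might infer that the trial has only 68% power; that holds only if Fisher is the primary test, which the expected counts make unlikely. The core point does not depend on the choice, since neither named test reaches 80% at 29 per arm.

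**Loss need not reduce power, and its frequency is unknown.** Both are true. A reader might infer that any lost patient lowers power. On the exact scale, one patient lost from one arm gives about 80% with chi-square, though at a type I error of about 6.2%. The equal-loss figures are illustrations.

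**Conclusion.** The concern holds in a limited form. Under the article's own assumptions (70% v 35%, two-sided 5%, 29 evaluable per arm), exact power is about 77% with the uncorrected Pearson chi-square. That is 2.6 points, or about two patients per arm, short of what is stated. The 68% for Fisher is conditional on a test that is unlikely to be chosen but is not ruled out. No allowance is made for patients without a discharge scan, although Box 1 foresees events after randomisation that would produce them and missing data are not imputed. Equal losses of two or three per arm would bring chi-square power to about 72% or 71%; those losses are assumed. The stated power should be corrected, but nothing in the design is invalidated.

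**What to change.** Wording only, in the Statistical analysis plan section:

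1. State the power as about 77% with 29 evaluable patients per arm, and about 71–72% with 26–27, for 70% v 35% under the uncorrected Pearson chi-square at two-sided 5%. Label the lower figures as assumed equal losses.
2. Name the uncorrected Pearson chi-square in advance as the single test of the primary endpoint, in place of the choice between two tests.
3. Disclose its exact type I error: 4.8% at 29 / 29 and a common rate of 52.5%, up to about 5.5% at other rates, and about 6.2% at 29 / 28.

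The cost is a slightly less favourable power statement and a primary test that can slightly exceed its nominal 5%. Fisher would avoid the excess (about 2.5% at 29 / 29) but would leave power at about 68%. No extra patients are needed for this correction. If the 80% is to be kept instead, about 31 evaluable patients per arm are needed with chi-square, plus whatever is set aside for loss.

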**Figure 2 F2:**
[figure not shown]
Therapeutic algorithm. Adapted from: Mullens *et al*
35 and Hollenberg *et al*.^36^ BP, blood pressure; CAVAL US, inferior vena cava and lung ultrasound; IV, intravenous; LCOS, low cardiac output syndrome; UO, urinary output.

All the patients will undergo lung and IVC ultrasound, independently of the group assigned during randomisation. Furthermore, an echocardiogram will be performed within 48 hours from admission according to the recommendations,^15^ as part of our standard of care.

A checklist will be made prior to hospital discharge to assess compliance with guideline-based treatment, vaccination, counselling and medical appointment after discharge. All patients will receive education by an HF nurse, who will provide educational material and drug treatment indications in a written grid.

Patients will be randomised into two arms and will be blinded to the assigned arm:

Control group: the treating medical team will be blinded to the lung and IVC ultrasound results. Patients will receive the standard of care of our centre and titration of diuretics will be based on standard practices (physical examination, symptoms and results of laboratory tests). The therapeutic goal (see figure 2) will be to discharge patients with relief of signs and symptoms of congestive HF, without ECG changes or abnormal laboratory findings that contraindicate hospital discharge. Circulating biomarkers of congestion are not part of the standard of care.Intervention group: the treating medical team will be unblinded to the lung and IVC ultrasound results. Patients will receive treatment for decongestion according to the results of the intervention plus the standard care (figure 2). The therapeutic objectives will be similar to the control group, with relief of the signs and symptoms of HF and additionally without congestion or mild residual congestion in the ultrasound test. At the discretion of the treating physician, the patient may be discharged when he or she shows mild to moderate signs of congestion in improvement with oral diuretics for more than 24 hours with adequate diuretic response.

Both groups will be scheduled to follow-up visits in our ambulatory clinic 7–10 days after discharge, and at least once per month.

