### Study endpoints and follow-up

The primary endpoint is the presence of subclinical congestion at discharge, defined as the presence of more than five B-lines and/or an increase in the diameter of the IVC, with and without collapsibility.

The secondary endpoint is the composite of readmission for HF, unplanned visit for worsening HF or death at 90 days. Additionally, we will assess other secondary endpoints such as the variation of pro-B-type natriuretic peptide at discharge, length of hospital stay, total number of HF hospital admissions and diuretic dose at 90 days (box 3). AHF hospitalisation was defined as unscheduled urgent hospital visit and hospital stay >24 hours, requiring intravenous HF therapies (diuretics, vasodilators, inotropes). Urgent AHF visits were defined as unscheduled visit to the emergency department resulting in increased dose of oral/intravenous therapy, stay <24 hours.

Box 3Secondary endpointsComposite outcome: readmission for heart failure (HF), unplanned visit for worsening HF or death at 90 days.All-cause mortality at 90 days.Duration of index hospital stay.Reduced total readmissions (first and recurrent) for HF at 90 days.Increased requirement for diuretics: patients who required a higher dose of furosemide compared with the dose indicated on hospital discharge.Pro-B-type natriuretic peptide (NT-proBNP) at discharge.% change of NT-proBNP (admission–discharge).

The safety endpoints during the index hospitalisation include:

Hypotension (systolic blood pressure <90 mm Hg).Requirement of vasoactive drugs (inotropic/pressor agents).Worsening renal function leading to a creatinine increase of ≥50% or >0.3 mg/dL on any of the blood tests performed during the index hospitalisation.Hypokalaemia <3.5 mmol/L or hyperkalaemia >5 mmol/L.

At 90 days after randomisation, two independent physicians, blinded to the assigned group, will adjudicate events by telephone contact. In case of disagreement, a third independent physician will evaluate the case.

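### The primary discharge proportion is compared without adjustment, so the continuous entry B-line count and IVC diameter, very probably available, are left unused: forgone precision, not an error

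*Protocol article*

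**What the plan says.** - **Endpoint** (Study endpoints and follow-up section): "The primary endpoint is the presence of subclinical congestion at discharge, defined as the presence of more than five B-lines"; an enlarged IVC, alone or in addition, also counts. It is a yes/no status read once, at discharge.
- **Test** (Statistical analysis plan): "The Χ^2^ test or Fisher’s exact test will be used to compare proportions". No covariate is attached to this comparison.
- **Adjustment** (same section): "multivariate Cox regression analysis will only be used if there are important prognostic factors", or baseline characteristics that differ significantly between the arms. No other adjusted analysis is described.
- **Sample size** (same section): 29 per arm, for "70% in usual care and 35% in the CAVAL US-guided strategy", with 80% power and a two-sided 5% error rate.
- **Ultrasound at entry**: Box 1 requires "Sufficient ultrasound visualisation to assess inferior vena cava and lungs" and excludes uninterpretable scans. Under Study intervention, "All the patients will undergo lung and IVC ultrasound, independently of the group assigned during randomisation", and the ultrasound protocol is part of the daily assessment of congestion. Scans are quantified off-line by readers blinded to arm (Lung and IVC ultrasound protocol).
- **Stratification** (Randomisation): age and left ventricular function only.

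**The concern.** The outcome is built from two measured quantities, B-line count and IVC diameter. How congested a patient is at entry is a natural predictor of how congested that patient is at discharge. Stratification does not balance it, and the primary test does not use it.

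The one adjusted analysis offered cannot fill the gap. A Cox model addresses time to an event, whereas this endpoint is a status at a single visit. Making adjustment depend on observed imbalance also means that the analysis is chosen after seeing the data.

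With 58 patients there is little power to spare, so a prognostic covariate that costs no new recruitment deserves a place if it is available.

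**Working it through.** **1. The plan's own figure.** Inputs from the Statistical analysis plan: p1 = 0.70, p2 = 0.35, two-sided 5%, power 80%. With the unpooled formula,

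n = (1.960 + 0.842)² × [0.70×0.30 + 0.35×0.65] / 0.35² = 7.849 × 0.4375 / 0.1225 = 28.03, rounded up to 29 per arm.

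The stated figure reproduces, and it is sized for two raw proportions.

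**2. Power of the planned tests at 29 per arm.** Chi-square: 77.5% by the pooled approximation, 77.4% by exact enumeration. Fisher: 68.4%. The chi-square figure is the reference below.

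**3. Room for chance imbalance.** The difference between arm means of a standardised baseline has SD √(2/29) = 0.263. A gap of at least 0.5 SD is 0.5/0.263 = 1.90 standard errors, which arises in about 6% of trials.

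**4. Which form of the baseline could help.** Patients enter with radiographic signs of congestion, so the yes/no definition is probably near 100% positive at entry. In a simulation with one latent outcome, adjusting for a yes/no baseline that was 90% positive gave power of 79%, 80%, 80% and 82% at correlations (rho) of 0, 0.3, 0.5 and 0.7. With 100% positive, nothing changes. Only the continuous values can add much.

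**5. Gain for the endpoint as defined.** Simulation with 29 per arm and 70% v 35%. There are two latent quantities (lung and IVC, assumed correlation 0.3), and a patient is positive if either crosses its threshold. Both entry values enter a linear model with arm. The documents give no rho, so a range is shown.

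| rho | Chi-square | Adjusted, ordinary SE | Adjusted, HC3 |
|---|---|---|---|
| 0 | about 77% | 76% | 74% |
| 0.3 | about 77% | 78% | 76% |
| 0.5 | about 77% | 82% | 80% |
| 0.7 | about 77% | 87% | 85% |

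The adjusted model rejected in 3.8–5.0% of trials under the null.

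**6. If rho differs by arm.** The intervention arm is treated towards no or mild residual ultrasound congestion, which may loosen the link between entry and discharge there. Chi-square v adjusted power:

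| rho control / intervention | HC3 | Ordinary SE (separate run, 8,000 replicates) |
|---|---|---|
| 0.5 / 0.2 | 77.0% v 76.8% | 78.2% v 79.3% |
| 0.7 / 0.2 | 76.7% v 78.0% | 78.1% v 80.8% |
| 0.5 / 0 | 77.6% v 76.2% | 77.0% v 77.3% |

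The change is −1.4 to +1.3 points with HC3 and +0.3 to +2.7 with ordinary standard errors.

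**The case against.** **The unadjusted test is valid and the trial was sized for it.** This stands. Chance imbalance is already inside its 5% error rate. A reader might infer that the trial loses planned power or that its result would be biased; the documents support neither.

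**The baseline reading is not documented.** This stands in part. Adequate visualisation is a statement about image quality, not a recorded count. No sentence says that a quantified scan is taken before randomisation, and Box 1 cannot date it, since it also lists events after entry such as death during the index stay. The readable-scan criterion, scanning in both arms, daily assessment and off-line quantification together make an entry reading very likely, but its timing must be confirmed. Adjusting for a scan taken after treatment had diverged would be wrong.

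**The gain may be small.** This stands. A simpler simulation, with one covariate and one latent outcome, suggests 13–14 points at rho 0.7, and a reader might quote that. It does not match an and/or endpoint with two covariates, where the gain is about 10 points at that rho and nil or slightly negative at rho 0.

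**Covariates may be left to a fuller document.** This carries less weight. The article names the test and says when adjustment is allowed, so the point concerns a stated choice rather than an omission.

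**Conclusion.** The point holds as a recommendation on efficiency. The planned comparison is sound but makes no use of the continuous entry B-line count and IVC diameter, and the only adjustment rule is both data-driven and of the wrong model type for this endpoint.

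The size rests on an assumed correlation. Adjustment changes power by about −1 point (rho 0), +1 (0.3), +5 (0.5) or +10 (0.7) with ordinary standard errors. It offers little if treating to an ultrasound target weakens the correlation in the intervention arm. The conclusion also assumes that a quantified pre-randomisation scan exists, which the article strongly implies but does not state.

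**What to change.** In the Statistical analysis plan section:

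- Name one primary analysis: a risk difference with 95% CI from a linear model with arm, log(1 + entry B-line count) and entry IVC diameter, fitted whatever the observed balance. State the standard error in advance. In these simulations ordinary standard errors kept the error rate, and HC3 cost about 2 points of power.
- Define the entry value as the scan acquired before randomisation and read by the blinded laboratory. If no such scan exists for the trial as a whole, leave the adjustment out.
- Keep patients with a missing entry value in the analysis, for example by a missing indicator or mean fill, and word this as an exception to the rule of no imputation.
- Retain the chi-square test as the supporting analysis, and drop the imbalance-triggered Cox model as a route to adjusting the discharge endpoint.

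The cost is wording, plus an off-line reading of the entry scan by a laboratory that already quantifies the trial's scans. The statistical price is two extra parameters and, if the entry values turn out not to be prognostic, up to about 1 point of power (about 3 with HC3).

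### The plan names Cox hazard ratios for the primary endpoint, which is a yes/no status at discharge with no event time; either the model does not fit or a secondary outcome is called primary

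*Protocol article*

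**What the plan says.** Study endpoints and follow-up (Protocol article) defines the main outcome: "The primary endpoint is the presence of subclinical congestion at discharge", judged from B-lines and/or IVC diameter. The same section adds: "The secondary endpoint is the composite of readmission for HF, unplanned visit for worsening HF or death at 90 days". The Abstract and Box 3 also list that clinical composite as secondary.

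The Statistical analysis plan sizes the trial on two proportions, "70% in usual care and 35% in the CAVAL US-guided strategy", with 29 patients per arm. For proportions, it says the chi-square "test or Fisher’s exact test will be used to compare proportions". Continuous variables go to the t-test or Mann-Whitney test.

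The next paragraph covers Kaplan-Meier and log-rank for time to first event, and then says: "Univariate HRs with associated 95% CIs will be estimated for the composite primary endpoint and secondary endpoints and derived from the Cox proportional-hazards model". Multivariable Cox regression is held in reserve for baseline imbalance, and 5% is the significance level throughout.

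Box 3's secondary endpoints include "Duration of index hospital stay", NT-proBNP at discharge and its percentage change, and total (first and recurrent) HF readmissions.

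**The concern.** A Cox model needs a time origin, an event time and a censoring rule. The discharge congestion status has none of these: each patient is read once, as yes or no. An analyst who follows the sentence must invent a time axis, and each obvious choice gives a poor answer.

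- **One common time for everyone.** The result then depends on how the software handles ties. One method gives an interval that is too wide; the other gives a hazard ratio that is not the planned relative risk.
- **Day of discharge as the time.** The hazard ratio mixes congestion with length of stay. Stay is itself a secondary endpoint, and it may differ by arm because the Study intervention section adds an ultrasound target to the intervention arm's discharge goal.

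What is at stake is the estimate and interval reported beside the primary test, and any adjusted estimate, since Cox is the adjusted model that the article names. The sentence also takes in secondary endpoints without limit, although several are not times to a first event.

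**Working it through.** **Inputs from the article.** Rates 0.70 and 0.35, 29 per arm, two-sided 5%, 80% power (Statistical analysis plan). The article gives no time axis, tie handling or length of stay; those used below are assumptions.

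**1. The plan's own figure.** Two-proportion formula with unpooled variance:

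n = (1.960 + 0.842)² × (0.70×0.30 + 0.35×0.65) / 0.35² = 7.849 × 0.4375 / 0.1225 = 28.03, rounded up to 29.

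This matches the article, so the trial was sized on a binary outcome.

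**2. Binary analysis at the planned result.** 29 × 0.35 and 29 × 0.70 are close to 10 and 20 events.

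- Risk ratio = (10/29)/(20/29) = 0.50. SE(log) = √(1/10 − 1/29 + 1/20 − 1/29) = 0.285. 95% CI = exp(−0.693 ± 1.96×0.285) = 0.29 to 0.87.
- Chi-square: pooled risk 30/58 = 0.517; z = 0.345/√(0.517×0.483×2/29) = 2.63; p = 0.009. Fisher p = 0.017.

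**3. Cox with one common time.**

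- *Breslow ties.* HR = 0.50. SE(log) = √(1/10 + 1/20) = 0.387. 95% CI 0.23 to 1.07, p = 0.07. The model variance is that of Poisson counts and omits the −1/29 terms. The interval includes 1 while chi-square gives p = 0.009.
- *Efron ties.* A fitted model gives HR 0.38, SE 0.389, 95% CI 0.18 to 0.82, p = 0.013. This agrees with the test but does not estimate the risk ratio. It lies near the ratio of cumulative hazards, ln(19/29)/ln(9/29) = (−0.423)/(−1.170) = 0.36.

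**4. Cox with discharge day as time.** Congested patients are events on their discharge day and the rest are censored then. Assumptions: log-normal stays with log-SD 0.5, Breslow ties, 29 per arm, and no true difference in congestion.

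| Congestion, both arms | Stay, intervention v control (days) | Median HR | False rejection |
|---|---|---|---|
| 52.5% | 8 v 6 | about 0.60 | about 24% |
| 52.5% | 6 v 8 | about 1.60 | about 24% |
| 70% | 8 v 6 | 0.61 | 33% |
| 70% | 6 v 8 | 1.64 | 32% |
| 70% | 6 v 6 | 0.99 | 3% |

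With a true 35% against 70% effect, stays of 8 v 6 days give a median HR of 0.31, and 6 v 8 days give 0.84 with 6% rejection. The hazard ratio moves with the difference in stay, in either direction.

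**5. Secondary endpoints.** The 90-day composite and 90-day mortality suit Cox. NT-proBNP and length of stay already have the t-test or Mann-Whitney. Total first and recurrent readmissions are a count, which a first-event Cox model does not analyse.

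**The case against.** **A valid primary test is already planned.** This stands. Chi-square or Fisher applies to the congestion proportions, and the Cox sentence speaks of estimating hazard ratios, not of replacing that test. A reader might infer that the trial's power falls from 77% (chi-square at 29 per arm) to 41%. The article does not support that: 41% belongs to a Cox Wald test with Breslow ties on a common time, which is nowhere named as the primary test. With Efron ties, rejection at the design effect is about 78%.

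**The wording may be a slip for the 90-day composite.** This is plausible. The sentence sits in the time-to-event paragraph, and where the trial defines its own endpoints the word composite is attached only to the 90-day outcome. Against it, the sentence lists secondary endpoints separately, and the congestion endpoint is itself an and/or combination. The article does not settle the intent, so one cannot say that the investigators mean to run Cox on discharge status. On the slip reading, the sentence still gives the primary label to an outcome defined as secondary.

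**The length-of-stay figures are assumed.** This stands. No stay is given, and the bias has no known direction. The simulation shows sensitivity, not a forecast.

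**A risk ratio or risk difference may be in an unseen plan.** This is fair, and its absence from the article is not the point. The point is that the article affirmatively names a method that does not fit.

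**The continuous secondary endpoints are covered.** This stands. It would be wrong to infer that NT-proBNP and length of stay have no suitable method; only total readmissions lacks a fitting one in the text.

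**Conclusion.** The sentence is wrong on either reading: it applies Cox to a discharge status without an event time, or it calls a secondary outcome primary. The damage is confined to the effect estimate, its interval and any Cox-adjusted estimate; the planned test of proportions and the sample size are unaffected.

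No time axis and tie rule tried gives both a sound estimate and a sound interval for the planned relative risk of 0.50. The Breslow standard error is 0.387 against 0.285, about 36% too large. Efron ties move the estimate to 0.38. Discharge-day time lets a two-day difference in stay produce a hazard ratio of about 0.60 or 1.60 with equal congestion. The common-time figures are exact for 10/29 against 20/29 and depend on the tie method; the discharge-day figures rest on the assumed stays and log-SD.

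**What to change.** Replace the sentence so that:

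- the primary endpoint is reported as a risk difference and/or risk ratio with 95% CI, beside the planned chi-square or Fisher test;
- any adjusted analysis of it uses a binary-outcome model in place of Cox;
- Kaplan-Meier, log-rank and Cox are limited to the 90-day time-to-first-event outcomes, namely the composite and all-cause mortality, both labelled secondary;
- NT-proBNP and length of stay remain with the continuous-variable tests already planned;
- total first and recurrent HF readmissions are analysed as a count rate.

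If the phrase was meant for the 90-day composite, correct the label as well. The cost is analysis wording only: no change to sample size, data collection or conduct.
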